**Visit 1: Screening Tests**

Prior to attending the screening visit, each potential participant will be asked to fast overnight (> 8 hours). This screening visit will be conducted under the NIA Uric Acid protocol number 2008-322. After the reviewing the study schema in detail and obtaining protocol, HIPAA, and HIV consents, potential participants will be screened for study eligibility by assessing medical history, physical examination, blood draw (26.5 ml), routine urinalysis, vital signs, height and weight (used to compute BMI) and waist circumference. EKG will be performed at baseline. Cognitive status will be assessed using the Blessed Mental Test and potential participant with a score> 3 will be excluded. Complete CBC with differential count, glucose, BUN, creatinine, UA, LDH, CPK, electrolytes (Na+, K+, Cl-; Ca++, Mg+), AST, ALT, ALP, albumin, globulin, bilirubin (total and direct), haptoglobin, HDL-LDL and Total cholesterol, triglycerides, and CRP will be estimated from blood samples. We will also test for HCV, HBV and HIV. The Glucose-6-Phosphate Dehydrogenase activity will be assessed in each eligible participant randomly assigned to Trial B (individuals who are glucose-6-phosphate dehydrogenase deficient cannot break down hydrogen peroxide, a byproduct of rasburicase, leading to hemolysis). In addition, we will tests potential participants for drug use (urine toxicology test). Urine analysis will be also performed to rule out urinary infections. Finally, urine pregnancy tests will be performed on all women of childbearing age. Since the average age of menopause in the U.S. in 51±4.1 years, all women under age 60 will be considered of childbearing age, with the exception of those who have had their uterus surgically removed. All these tests are aimed at screening for conditions that are considered exclusion criteria for this study, and are performed according to standard clinical methods. A physician will review subject’s medical history, physical exams, EKG and biological tests in order to evaluate the participant’s eligibility criteria. Subjects who are found to be eligible for the study will be scheduled for Visit 2. Those assessed as ineligible will be notified within one week. When notified of eligibility, participants will be instructed on NPO criteria for Visit 2. The participants will receive the following instructions written on an hand-out: 1. To maintain the same dietary habits they had before being involved in the study; 2. In particular not to change their dietary habits by increasing high-purine sea foods, such as anchovies, sardines, herring, mackerel, and scallops, high-purine meats, such as game meats, liver, beef, kidney, brains, meat extracts (e.g. Oxo, Bovril), meat gravys, pork, poultry, and sweetbreads, and high-purine vegetables, such as asparagus, green peas, cauliflower, spinach and mushrooms, lentil, dried peas and beans, and to continue to consume vegetables, oatmeal, wheat bran and wheat germ in the same portions as before. Participants will be advised that changes in their habitual diet may result in a substantial change of their circulating UA levels and that, if so, their participation in the study will be discontinued.

**Visit 2: history, physical exam and preliminary test**

Participants will arrive at NIA Clinical Research Unit after overnight fasting for 8 hours. A brief physical examination will be performed, including a sample of blood that will be collected for DNA extraction and characterization of the genes that indirectly or directly affect the UA metabolism. A physician will review subject’s eligibility criteria and immediately after the participant will be administered an MRI-spectroscopy that estimates the rate of phosphocreatinine resynthesis after exercise). Next, an Oral Lipid Tolerance Test (OLTT) will be performed. The OLTT consists of eating a standard fast-food type meal (with approximately 900 cal and 50 grams of fat), and measuring changes in lipids and inflammatory markers at 2 hour intervals for total of 8 hours. The meal will be prepared by a registered dietitian and will be consumed in no longer than 20 minutes. The inflammatory markers that will be sampled consist of IL-6, IL-6sr, TNF-α, TNF-r1, TNF-r2, sgp 130, and hsCRP (+Tryglycerides). However, based on the information available at the end of the study, some of these inflammatory markers may not be measured and may be substituted with markers without changing the quantity of blood collected. OLTT will start in the morning after 8 hours of fasting. After the meal, subjects will not eat for the next 8 hours but will have free access to water and ice. After 8 hours a standard meal will be available. Blood samples will be drawn before the meal and every 2 hours after the first bite of the meal over an 8-hour period. The total amount of blood needed for the tests/assays included in the OLTT will be 40 mL including a 1mL waste at each time point. The blood will be sent via courier to NIA Lab at the 2 hour intervals. From there the blood will be sent to the respective labs for processing. After discharge, the patient will be given instruction for the following visit. In particular, participants will be advised to drink 8 8oz glasses of water on the day before the visit and at least 2 further glasses in the morning before the infusion.

**Visit 3: Baseline and short-term post-intervention**

Visit 3 will be scheduled at least 2 days after Visit 2. Participants will be asked to arrive the evening before Visit 3 for a two consecutive overnight stay at the NIA Clinical ResearchUnit. Below is the sequence of exams and blood tests scheduled for Visit 3. As mentioned above, participants will be requested to drink at least two glasses of water and eat a light breakfast (cold cereal, milk, coffee or tea and bread and butter with butter and/or jelly in the morning). If for some reason, the study participant does not consume an appropriate amount of water on their own 500 mL of normal saline 0.09% will be administered intravenously prior to the study intervention. Based on their characteristics (UA serum level) and sequence of enrollment, participant will be assigned a randomization envelope. After opening the envelope and compiling the included randomization form, the NIA research pharmacist assigns the participant to the treatment or placebo group and prepares the study drug. Information on randomization will be maintained by the NIA research pharmacy in a safe but known place, accessible in case of emergencies. At 4:00 pm following the treatment, participants will eat a dinner consisting of a sandwich and a bag of chips. They may have a soda, coffee, tea or milk. The participant will be not be able to eat again until morning for the lipid tolerance test but will be given water freely.

*1. Basal Metabolic Rate (BMR)*

Basal Metabolic Rate will be estimated in Visit 3 at baseline and on the next day after the intervention. The measurement will be performed in the morning after overnight fasting at the NIA Clinical Research Unit. RMR will be measured before any other evaluation using the COSMED K4 b2 portable indirect calorimeter.

*2. Vital sign measurements*

Blood pressure, pulse rate, respirations and core body temperature will be measured at baseline and at each evaluation time during the following 24 hours. Pulse rate and blood pressure will be estimated using an automated cuff. Core temperature will be estimated using a sublingual thermometer. An EKG will be obtained 24 hours after the beginning of the infusion.

*3. Infusion of the Study Drug*

In Trial A (Uric Acid vs Placebo), infusion of the drug will be started only if the specific gravity of the urine is less than 1.015. In both trials A and B, treatment or placebo will be infused using an IV infusion pump over a 60 minute time period. When the infusion is completed the line will be discontinued.

After the infusion of the study drug, participants will be encouraged to drink at least 8 8oz glasses of water over the next 12 hours. However, if they are unable to drink enough water, 1000 mL of saline solution will be administered intravenously. To obtain mildly alkaline urine, all subjects enrolled in Trial A will receive 7 oral doses of 650 mg sodium bicarbonate (total 4,550 mg = 54.6 mEq) according to the following timeline: 1 tablet in the evening before Day 1 of Visit 2; one tablet in the morning of visit 2; one tablet at the beginning of study drug administration: one tablet 4, 8, 12 and 24 hours after the study drug administration.

*4 Blood sampling*

Baseline fasting blood sampling will be done using an IV access different from the one used for infusing the study drug. An intravenous cannula will be inserted into a large vein using a standard aseptic technique and, if requested from participants, a local anesthesia. The IV site will be kept open by a KVO rate for continuous saline solution infusion, and will be used to draw blood samples. The cannula will be removed at the end of this visit. The total amount of blood drawn for this visit is 256.5 mL including 1 mL waste at each timepoint, and the breakdown is listed below. During the infusion the samples for the following tests will be collected: uric acid and hypoxanthine (monitoring), inflammatory markers, circulating antioxidants, markers of oxidative damage and RNA expression. Some of the blood collected will be used to create aliquots of serum and plasma that will be stored to measure other biomarkers relevant for this study based on the most current literature.

*5. Inflammatory markers*

Blood samples for measuring proinflammatory markers will be collected at baseline and after 1, 2, 4, 8, 12, and 24 hours after the beginning of the infusion. At each of the successive blood sample draws, IL-1ra, IL-6, IL-6r, IL-18, IL-1β, TNF-α, TNF-r1, TNF-r2, sgp130 and hsCRP will be assessed in duplicate using high sensitivity ELISA assays. Based on the information available at the end of the study, some of these inflammatory markers may not be measured and may be substituted with markers without changing the quantity of blood collected. The total amount of blood per each time we perform these assays will be 3.5 mL.

*6. Circulating Antioxidant markers*

Participants will be tested for Vitamin C, Carotenoids and Selenium at baseline and each of the successive blood sample draws. Serum levels of vitamin C will be assayed using HPLC with 1-methylUA used as an electrochemically active internal standard. Serum levels of carotenoids will be determined by high performance liquid chromatography (HPLC). Selenium will be measured by graphite furnace atomic absorption spectrometry using a Perkin Elmer Analyst 600 with Zeeman background correction. The total amount of blood per each time we perform these assays will be equal to 4.5 mL.

*7. Markers of Oxidative Damage*

Participants’ blood samples will be tested for markers of oxidative stress damage, including but not limited to F2-Isoprostane (marker of lipid peroxidation) and oxidized/reduced glutathione ratio at baseline and after 1, 2, 4, 8, 12, and 24 hours from the beginning of the infusion. Based on the information available at the end of the study, other emerging more reliable markers of oxidative stress may be also measured without changes in the quantity of blood collected.

*8. RNA microarray expression*

Whole Blood samples for microarray RNA expression will be collected on PAXgene (QIAGEN/BD) tubes at baseline, and at 12 and 24 hours after the beginning of the infusion.

*9. Uric Acid*

A uric acid and hypoxanthine level will be measured level will be measured at baseline, after 1, 2, 4, 8, 12 and 24 hours and after 2 weeks after the beginning of the infusion. Approximately 3.5mL of blood will be drawn for this at each time-point.

*10. Follow up Blood work*

Total and differential white and red blood counts, hemoglobin, hematocrit, platelets, glucose, BUN, creatinine, Uric Acid, LDH, CPK, electrolytes, AST, ALT, ALP, albumin, globulin, bilirubin (total and direct), haptoglobin, HDL and total cholesterol, triglycerides, and CRP will be drawn at the 24 hour timepoint to make sure that there has been no change post intervention. The total amount of blood needed for this will be 15 mL.

*11. Urine collection*

A urine sample will be collected at baseline (first morning void on Day 1), every void between 1 and 12 hours after infusion and 24 hours after infusion. The urine samples will be used to evaluate uric acid levels in the urine and potentially markers of oxidative stress damage.

*12. MRI muscle spectroscopy.*

Magnetic resonance spectroscopy (MRS) will be used to study energy metabolism in muscle during and after exercise. As already mentioned, MRS is performed once on Visit 2 and a second time 24 hours after the infusion of the study drug, immediately before performing the second Lipid Tolerance Test. Participants will be carefully screened for MRI contraindications before performing the tests. Also, they will be given a choice of receiving the MRI. Participants with contraindication to MRI or refusing MRI will not receive MRI but will be still enrolled in the other parts of the study, without any effects on their compensation.

*13. Lipid Tolerance Test*

24 hours after the injection, A second OLTT will be performed using exactly the same protocol used in Visit 2.

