**Trial B: Rasburicase versus Placebo**

Treatment: Rasburicase 0.15 mg/kg in 250 ml 0.9% sodium chloride solution infused over a 60 minute period on visit 3.

Placebo: 250 ml of 0.9% sodium chloride solution infused over a 60 minute period on visit 3.

Both treatment and placebo administration will be done only once and according to the same procedures. Treatment and placebo administration will be done in double-blind fashion and under continuous physician’s supervision. Only the NIA research Pharmacist or someone designated by him will be aware of the participant random assignment to treatment or placebo.

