**14. PHARMACEUTICAL INFORMATION**

**Uric Acid**

Description: UA I.V. solution is manufactured by Florida Biologix, Center of Excellence for Regenerative Health Biotechnology, University of Florida, USA (see ***Appendix A***). The description of UA chemistry and physiology in humans is reported in ***Appendix B***.

Dose: UA 500 mg in 250 ml of 0.1% lithium carbonate/4% dextrose solution will be administered intravenously over a 60 minute period. Before administration and on the same day, UA solution will be filtered for both UA microcrystals using a 0.22 mm Millex filter (Millipore, Molsheim, France), and for virus using the Millipore Viresolve NFR  (OptiScale-25 Small Volume Disposable Capsule Filter). The Millipore in-line filter will be done generating the required 20-50 psi of pressure for fluid passage that will be created using a peristaltic pump. The vehicle was selected because it allows stable dissolution of UA and theoretically should not affect serum antioxidant capacity.

Route of Administration: intravenous administration of reconstituted formula.

Clinical pharmacology: UA was administered intravenously in two previous clinical studies conducted at the Clinical Pharmacology Unit and research Center, The University of Edinburgh, UK. Infusion of 1,000 mg of UA in a 500 ml 4% dextrose/0.1% lithium carbonate vehicle led to a time-dependent UA increment of about 3.2-4.9 mg/dL. Serum UA concentration exhibited a two-component decay with a mean elimination half-life of 10.8 h. The elimination and distribution phase after infusion of 1,000 mg of UA has been previously described (16).

Drug Interactions: no data are available.

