Rasburicase has been used in France and Italy for almost 3 decades. An international report from Bosly et al. showed that in 112 adult patients (28%) (31 were older than age 65 years) affected from malignancies, such as acute myeloid leukemia (38%) and non-Hodgkin lymphoma (29%), the reduction of plasma UA to normal levels within 4 hours was quite similar for adults and children in both the prophylaxis and treatment (52). Rasburicase was well tolerated, with mild headache being the most common side effect. Similar results are from the U.S. compassionate access program (53) and from a completed Phase II study in adult patients with lymphoma (50) constituting a substantial body of evidence regarding the efficacy and safety of rasburicase in adults.

Indication for Use: Rasburicase is administered as a 30-minute infusion once daily at a dose of 0.15 or 0.20 mg/kg/day (maximum total daily dose 0.20-0.40 mg/kg/day) in the initial management of higher plasma UA levels in pediatric patients with leukemia, lymphoma, and solid tumor malignancies who are receiving anti-cancer therapy.

Dose : All participants in this study will be administered a single dose of Rasburicase equal to **0.15 mg/kg/day** intravenously over 60 minutes. The product reconstituted with diluent is a clear, colorless solution. The reconstituted solution will not be shaken and will be inspected visually for particulate matter and discoloration prior to administration. The solution will be diluted in 250-mL of preservative-free NaCl 0.9% and is infused over 60 minutes without filtration. The reconstituted rasburicase must be administered within 24 hours of reconstitution.

Note that the dose of **0.15 mg/kg/day** is substantially lower that the dose already approved from FDA in pediatric and adult patients. This cautious approach was selected because we do not have sufficient data to determine whether geriatric subjects respond differently from pediatric subjects to rasburicase administration.

Route of Administration: intravenous administration of reconstituted formula.

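### The pre-infusion hydration order names normal saline but prints a strength of 0.09%, one tenth of the 0.9% sodium chloride stated everywhere else in the protocol

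*Protocol*

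**What the plan says.** The order is in Section 5 of the protocol, under Visit 3. Participants are told to drink water on the morning of the infusion. The fallback opens with the condition "If for some reason, the study participant does not consume an appropriate amount of water on their own" and continues with the instruction "500 mL of normal saline 0.09% will be administered intravenously prior to the study intervention". It is not limited to one trial, and Section 5 says that both trials follow the same clinical and laboratory procedures.

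Three other places print a sodium chloride strength:

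- Section 5, Trial B, active arm: "Treatment: Rasburicase 0.15 mg/kg in 250 ml 0.9% sodium chloride solution infused over a 60 minute period on visit 3".
- Section 5, Trial B, placebo arm: "Placebo: 250 ml of 0.9% sodium chloride solution infused over a 60 minute period on visit 3".
- Section 14, rasburicase, Dose: "The solution will be diluted in 250-mL of preservative-free NaCl 0.9% and is infused over 60 minutes without filtration".

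Two other uses of saline at Visit 3 carry no strength. One is the fallback after the infusion, "1000 mL of saline solution will be administered intravenously". The other is the slow saline flow that keeps the sampling line open.

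**The concern.** Two parts of one intravenous order disagree. The fluid is named as normal saline, yet the percentage beside the name is a tenth of the sodium chloride percentage used in the rest of the protocol. Someone preparing the bag has to decide whether the name or the number governs, and the protocol gives no rule for deciding.

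What is at stake is that a supportive-care instruction can be carried out in two ways. It is operative text, not background, and it is the only hydration instruction in the protocol with a stated strength. It applies to community volunteers aged 50 to 75 who, according to Section 17, are not expected to gain direct medical benefit. That justifies correcting it even though a pharmacist may well notice the mismatch.

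**Working it through.** The protocol derives no figure on this point, so there is none to reproduce. The check compares the printed strengths and converts each to an amount of solute.

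**Inputs from the protocol**

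- Volume in the Visit 3 pre-infusion order: 500 mL = 0.5 L.
- Strength printed in that order: 0.09%.
- Strength printed in both Trial B infusions and in the rasburicase dilution instruction: 0.9%.

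**Inputs not from the protocol**

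- The percentages are read as weight per volume, so 1% = 10 g/L.
- The molar mass of sodium chloride is 58.44 g/mol, a physical constant. Theoretical osmolarity is taken as 2 × mmol/L.

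**Ratio**

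0.9 / 0.09 = 10. The difference is exactly tenfold.

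**Conversion**

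| Quantity | At 0.09% | At 0.9% |
| --- | --- | --- |
| g/L = percent × 10 | 0.9 | 9 |
| g in 500 mL = g/L × 0.5 | 0.45 | 4.5 |
| mmol/L = g/L ÷ 58.44 × 1,000 | 15.4 | 154 |
| Theoretical mOsm/L = 2 × mmol/L | about 31 | about 308 |

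These figures describe the contents of the bag. They are not an estimate of any effect on a participant or on a laboratory value.

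**Does other text settle the matter?**

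- The Trial B and rasburicase passages agree with one another at 0.9%. They describe the study infusions, however, and not hydration, so they do not formally define the fluid in the Visit 3 order.
- The Trial A vehicle is a lithium carbonate and dextrose solution, which gives no sodium chloride strength to compare.
- The 1000 mL post-infusion fallback and the keep-open line state no strength. They neither confirm nor contradict 0.09%.
- No footnote or later section corrects the number. It is printed as plain digits in running text, which does not look like a broken table, a redaction or a lost symbol.

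The conflict therefore lies first inside the one phrase, and secondly between that phrase and the three other stated strengths.

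**The case against.** The best reply is that this is a decimal slip and nothing more. The order gives the product by name, pharmacy staff would very probably query the number, and only participants who under-drink are affected. Participants are told to drink eight glasses of water the day before and at least two on the morning, and they stay at the unit from the previous evening, so the fallback may rarely be used. The protocol gives no figure for how often. Most of this stands and limits the weight of the point. It does not remove the point: an intravenous order should not rely on someone noticing that its name and its concentration disagree tenfold.

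It is also fair to say that the 1000 mL post-infusion instruction is not part of the contradiction. It states no strength and so conflicts with nothing. Adding one there would be a matter of preference.

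A reader might go further and infer that the fluid would disturb LDH, bilirubin and haptoglobin, the markers that a footnote to the rasburicase safety text assigns to monitoring for haemolysis, and so blur attribution in a trial with 10 participants per arm. The documents do not support that. No passage links the hydration fluid to haemolysis, and nothing gives a size of effect for 500 mL. The footnote concerns rasburicase, whereas the hydration order covers both trials. The order also precedes the study infusion, is the same for both arms, and is applied with participants and investigators blinded. Under-drinking beforehand cannot depend on the treatment then received. Chance imbalance between small arms is possible, but systematic bias is not shown.

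**Conclusion.** The contradiction is real and exactly tenfold: normal saline by name and 0.09% by number, against 0.9% in each of the three other places where a sodium chloride strength is printed. Nothing in the protocol resolves it. The size of the conflict rests only on the printed percentages; the gram and osmolarity figures also need the weight-per-volume reading and the molar mass given above.

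This is a minor correction with a bearing on safety. It touches no endpoint, sample size, power figure, randomisation step or analysis.

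Two stronger readings should be resisted. One is that, as written, participants receive a fluid close to plain water. That follows only if the number is preferred to the name, and the order does not say which governs. The other is that Section 14 contains a companion error, because it states the pore size of the uric acid filter in millimetres ("UA solution will be filtered for both UA microcrystals using a 0.22 mm Millex filter"). A micro sign lost when the text was read from the PDF would explain that unit, so it is not evidence of an error in the plan, and nothing here depends on it.

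**What to change.** Reconcile the pre-infusion order under Visit 3 with the Trial B treatment and placebo descriptions in Section 5 and the rasburicase dose text in Section 14, so that the order names one fluid with one concentration. Then check the pharmacy order sheet for Visit 3 against the amended wording. The choice of fluid and strength belongs to the sponsor and the responsible clinicians; this review does not make it.

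The cost is a one-line amendment and one order-sheet check. No statistical section needs to change.

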**Trial A: UA versus placebo**

Treatment: UA 500 mg in 250 ml of 0.1% lithium carbonate/ 4% dextrose solution infused over a 60 minute period on visit 3.

Placebo: 250 ml of 0.1% lithium carbonate/ 4% dextrose solution infused over a 60 minute period on visit 3.

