**Clinical and laboratory procedures in both trials**

The clinical and laboratory procedures will be articulated into two main steps. The first part will be a screening of the potential participants, while the second part will be a comprehensive assessment of participants’ clinical characteristics and collection of blood samples. Blood drawn during the screening visit will be sent to Harbor Hospital. On subsequent visits, sample for assay of the inflammatory markers will be sent to the core lab, divided into aliquots banked at the NIA’s Core Lab, and at the end of the study sent to the different laboratories to perform the appropriate assays.

|  | **Visit 1**  **(T0)** | **Visit 2**  **(T1)** | | | | | | **Visit 3**  **Inpatient**  **(T2)** | | | | | | | | | | | | | **Visit 4**  **(T3)** |
| --- | --- | --- | --- | --- | --- | --- | --- | --- | --- | --- | --- | --- | --- | --- | --- | --- | --- | --- | --- | --- | --- |
|  | Outpatient | Outpatient  (up to 1 week after Visit 1 and 2 days before Visit 3) | | | | | | Day 1 | | | | | | | Day 2  (24 h from intervention is the baseline for the second Oral Lipid Tolerance Test) | | | | | | Outpatient |
| **Type of Visit** | Screening | Baseline | 0h | 2h | 4h | 6h | 8h | Baseline | Intervention | 1 h | 2 h | 4 h | 8 h | 12 h | 24 h | 0 h | 2 h | 4 h | 6 h | 8 h | 2 weeks |
| Medical History/  Physical Exam | X | X |  |  |  |  |  |  |  |  |  |  |  |  |  |  |  |  |  |  | X |
| EKG | X |  |  |  |  |  |  |  |  |  |  |  |  |  | X |  |  |  |  |  | X |
| HIV, HBV, HCV | X |  |  |  |  |  |  |  |  |  |  |  |  |  |  |  |  |  |  |  |  |
|  |  |  |  |  |  |  |  |  |  |  |  |  |  |  |  |  |  |  |  |  |  |
| Blood tests1 | X |  |  |  |  |  |  |  |  |  |  |  |  |  | X |  |  |  |  |  | X |
| Urine analysis | X |  |  |  |  |  |  |  |  |  |  |  |  |  |  |  |  |  |  |  | X |
| Urine Toxicology2 | X |  |  |  |  |  |  |  |  |  |  |  |  |  |  |  |  |  |  |  |  |
| Urine Pregnancy | X | X |  |  |  |  |  | X |  |  |  |  |  |  |  |  |  |  |  |  |  |
| Urine Specific Gravity |  |  |  |  |  |  |  | X |  |  | X |  |  |  | X |  |  |  |  |  |  |
| Urine PH |  |  |  |  |  |  |  | X |  |  | X |  |  |  | X |  |  |  |  |  |  |
| Urine for Uric Acid |  |  |  |  |  |  |  | X |  | X | | | | | X |  |  |  |  |  | X |
| Eligibility, Consent | X |  |  |  |  |  |  |  |  |  |  |  |  |  |  |  |  |  |  |  |  |
| Randomization |  |  |  |  |  |  |  | X |  |  |  |  |  |  |  |  |  |  |  |  |  |

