**6. RISKS/DISCOMFORTS**

Risk associated with the administration of UA solution: UA is a physiological constituent of cells and blood in humans. Based on published studies, I.V. administration of UA 1,000 mg and 500 mg in 250 ml of 0.1% lithium carbonate/ 4% dextrose solution over a 60 minute period was not associated with any adverse event, change in blood pH, clinical, hemodynamic and biochemical parameters. In a total of 44 persons, the administration of UA 500 mg was associated with an average increase of circulating levels between 3 and 4 mg/dL which creates a transitory increase of the UA concentration. The transitory increase of the UA concentration did not cause any risk, while it was associated with increased plasma antioxidant activity, reduced oxidative stress marker and better endothelial function. There is a very low risk that UA may precipitate in renal tubules and cause kidney damage. This risk is minimized by administering a dose of UA that should not increase the UA concentration above the solubility threshold, checking the urine specific gravity is below 1015 before the administration, ensuring abundant intake of water, inducing a mild urine alkalinitation (by administering orally sodium bicarbonate) and monitoring the urine pH and specific gravity.

Risk associated with the administration of Rasburicase: Potential side effects are listed in the table below. These side effects have been observed in 703 patients affected from leukemia, lymphoma, and solid tumor malignancies who are receiving anti-cancer therapy. The most severe side effects of Rasburicase administration are hypersensitivity reactions including anaphylaxis (<1%), and methemoglobinemia (<1%).

| **Serious Adverse Reaction** | Percentage (%) of Subjects (total n=703) |
| --- | --- |
| Allergic reactions including anaphylaxis | <1 |
| Rash | <1 |
| Hemolysis | <1 |
| Methemoglobinemia | <1 |
| Fever | 5 |
| Neutropenia with fever | 4 |
| Respiratory distress | 3 |
| Sepsis | 3 |
| Neutropenia | 2 |
| Mucositis | 2 |
| **Adverse Reaction** | Percentage (%) of Subjects (total n=436) |
| Vomiting | 50 |
| Fever | 46 |
| Nausea | 27 |
| Headache | 26 |
| Diarrhea | 20 |
| Mucositis | 15 |
| Rash | 13 |

Note: an antibody response to a single dose of rasburicase (immunogenicity) has also been observed. To the date of this protocol, the immunogenicity issue is not applicable to our study since the drug is not approved for the treatment of adults.

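### The Trial A bicarbonate timeline ties the first two tablets to Visit 2 instead of Visit 3, so as written no tablet falls between the morning of Visit 2 and the start of the infusion

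*Protocol*

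**What the plan says.** Protocol section 5, Visit 3, item 3 (Infusion of the Study Drug) gives every Trial A participant seven 650 mg sodium bicarbonate tablets, 4,550 mg or 54.6 mEq in total. The first two are scheduled as "1 tablet in the evening before Day 1 of Visit 2; one tablet in the morning of visit 2". The third is taken when the study drug is started, and the other four follow at 4, 8, 12 and 24 hours.

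The rest of the protocol places the infusion at a different visit:

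- Section 5, Trial A: the uric acid or placebo solution is "infused over a 60 minute period on visit 3".
- Section 5, Visit 3: "Visit 3 will be scheduled at least 2 days after Visit 2". The Visit 2 column of the schedule table agrees: "up to 1 week after Visit 1 and 2 days before Visit 3".
- Section 5, Visit 3: "Participants will be asked to arrive the evening before Visit 3 for a two consecutive overnight stay".

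Section 6 explains the tablets. Among the measures that reduce the risk of uric acid precipitating in the renal tubules it lists "inducing a mild urine alkalinitation (by administering orally sodium bicarbonate) and monitoring the urine pH and specific gravity". The only stated condition for starting the Trial A infusion is in item 3: "infusion of the drug will be started only if the specific gravity of the urine is less than 1.015".

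The Visit 3 section also says that, for a participant who has not drunk enough water, "500 mL of normal saline 0.09% will be administered intravenously prior to the study intervention".

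**The concern.** The tablets are meant to make the urine mildly alkaline around a uric acid load. Tablets one and two are the only ones scheduled before the infusion begins, and both carry the label of a visit held at least two days earlier. Staff who follow the text as written would give no bicarbonate in the days just before the infusion. The third tablet is taken as the infusion starts, so none of the alkalinization would be in place beforehand.

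What is at stake is a renal safety step, not the trial's inference. This is a dosing instruction that staff work from, and nothing later in the procedure requires them to notice that the pre-infusion tablets were given on the wrong days.

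**Working it through.** **1. Dose count.** The timeline gives 1 + 1 + 1 + 4 = 7 tablets, and 7 × 650 mg = 4,550 mg. This reproduces the protocol's total, so the error lies only in the visit label.

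**2. Which visit is meant.** Setting the tablet instruction beside the visit structure:

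| Feature of the instruction | Visit 2 | Visit 3 |
|---|---|---|
| Study drug infused | No | Yes (section 5, Trial A) |
| Has a Day 1 | No; one outpatient day (schedule table) | Yes; Day 1 and Day 2 |
| Participant at the unit the evening before | No; arrives after an overnight fast | Yes; arrives the evening before |
| Section containing the instruction | No | Yes |

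Every row points to Visit 3. No other text gives a bicarbonate schedule that would override this one. The schedule tables have no bicarbonate row, and the participant instructions under Visits 1 and 2 cover diet, fasting and water only.

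**3. Share of the dose affected.** From the protocol's own total, 54.6 mEq / 7 = 7.8 mEq per tablet.

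- Misplaced: 2 × 650 = 1,300 mg; 2 × 7.8 = 15.6 mEq; 2/7 = 28.6%.
- Correctly placed: 5 × 650 = 3,250 mg; 5 × 7.8 = 39.0 mEq; 5/7 = 71.4%.

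**4. Timing before the infusion.** The protocol gives no clock times. Assume an evening tablet at 20:00, a morning tablet at 07:00 and an infusion start between 08:00 and 12:00.

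- Visit 3 as the intended visit: the evening tablet precedes the infusion by 12 to 16 h and the morning tablet by 1 to 5 h.
- Visit 2 as written, at the two-day minimum: add 48 h to each. The evening tablet precedes the infusion by 60 to 64 h and the morning tablet by 49 to 53 h. A longer interval between the visits widens the gap further.

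Other plausible clock times move these figures by a few hours. They do not change the finding that the last pre-infusion tablet is about two days early or more.

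**5. Would the procedure catch it?** The schedule table has urine pH measured at the Visit 3 baseline, but no pH threshold is attached to starting the infusion. The specific gravity check measures urine concentration and says nothing about alkalinity.

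**6. Saline.** Section 5 (Trial B) and the rasburicase dose paragraph in section 14 both give sodium chloride as 0.9%. The Visit 3 figure is smaller by 0.9 / 0.09 = 10-fold and contradicts the name normal saline beside it. It is a decimal slip.

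**The case against.** The best reply is that the literal reading cannot be carried out. Visit 2 has no Day 1, nobody stays at the unit the night before it, and the sentence sits among the infusion instructions. The schedule tables label Visit 3 as T2, which may be how the slip arose. A competent team would read Visit 3. Even if it did not, five of the seven tablets run from the start of the infusion to 24 h. Section 14 gives uric acid a mean elimination half-life of 10.8 h, so those five cover much of the period in which the load is cleared. The limited dose, hydration, specific gravity check, urine monitoring and physician supervision all remain, and a low baseline pH would be visible to staff. The saline slip is unrelated and corrected by its own wording.

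Most of this stands, and it limits the point. The intended visit can be inferred, harm is unlikely, and the saline slip adds no weight to the bicarbonate point. What does not follow is that the text can be left alone. It is the only bicarbonate schedule in the protocol. Staff must either depart from it without saying so or give the tablets on the wrong days. A pH value that may be noticed is weaker protection than one that must be met.

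**Conclusion.** The concern holds. The visit number is wrong in both places where the pre-infusion tablets are scheduled. As written, 2 of 7 tablets (1,300 of 4,550 mg; 15.6 of 54.6 mEq; 29%) are assigned to a visit at least two days before the infusion, and no tablet falls between the morning of Visit 2 and the start of the infusion. That all pre-infusion alkalinization is lost assumes that staff follow the text literally; the hour figures rest on assumed clock times.

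The consequence is confined to one of several renal precautions, against a risk that section 6 calls very low. All Trial A participants take the same tablets, so the randomised comparison is not biased, and sample size, power and analysis are untouched. It merits correction because it is an operative dosing instruction for a stated safety measure and no pH limit stands behind it. The 0.09% saline figure is a separate, smaller error in an intravenous order.

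**What to change.** In section 5, Visit 3, item 3, change the visit number from 2 to 3 in both places, so that the first tablet is taken on the evening before Day 1 of Visit 3 and the second on the morning of Visit 3. The total stays at 7 tablets and 4,550 mg, and the evening tablet then coincides with the planned arrival at the unit. In the opening paragraph of the Visit 3 section, change 0.09% to 0.9%.

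The cost is three substitutions, carried over to any order sheets or site instructions prepared from this text. Design, dose, sample size and analysis do not change.
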